**Fig. 2 Fig2:**
[figure not shown]
Programme logic model of the Goldilocks-childcare randomised controlled trial. The dashed oblong represents the overall programme logic for the Goldilocks work principle. The golden box represents the input, the light blue boxes the intended steps at an organisational level, and the dark blue boxes the intended steps at an individual level. The black boxes illustrate the process evaluation. The middle row (Cardiorespiratory fitness) shows how the intervention will expectedly lead to improved cardiorespiratory fitness. The bottom row (Process evaluation) illustrates how the ‘black box’ between each step of the programme will be evaluated. Heart rate (HR) reserve is defined as the difference between the estimated maximal heart rate and the heart rate during sleep

### Delivery of intervention

Work environment consultants (Physiotherapists and Occupational therapists) from the Work Environment Consultancy of Copenhagen Municipality (WECoCM) will deliver the intervention components (workshops and visits). In order to ensure a consistent delivery across the participating institutions, we have developed an intervention protocol describing all intervention components.

### Intervention content

Figure 3 provides an overview of the intervention components. At each individual childcare institution, the intervention will be initiated by a two-and-a-half-hours workshop (Workshop 1) during a regular staff meeting. At Workshop 1, the work environment consultants will inform the participating Trio and childcare workers about the overall concept of the Goldilocks work principle, facilitate that the participants develop tailored Goldilocks-games compliant with their pedagogical teaching goals, and finally develop specific action plans allocating responsibilities for implementation of the Goldilocks-games in their daily routines and schedules. Information regarding whether the Goldilocks-games were conducted as planned will be collected.

**Fig. 3 Fig3:**
[figure not shown]
Overview of intervention components. Trio = the group at each of the participating institutions consisting of a manager, a union representative, and an occupational health and safety representative. MVPA = Moderate to Vigorous Physical Activity

After three to four weeks of the intervention period, the work environment consultants will conduct a one-and-a-half-hour follow-up workshop (Workshop 2) with the participants at each individual childcare institution. The aims will be to i) evaluate the implementation of the Goldilocks-games, ii) facilitate sustainability of well-functioning Goldilocks-games, and iii) modify those Goldilocks-games, which are not working as intended. Moreover, in order to facilitate implementation of the Goldilocks-games, the work environment consultants will make a consultation visit at the childcare institution 2 weeks after Workshop 1 and have a consultation phone call with a member of the Trio 2 weeks after Workshop 2.

### Control group

Institutions in this group serve as waitlist controls. Thus, institutions in the control group will continue their usual practice for the first 10 weeks, while institutions in the intervention group implement the intervention. Following the 10-week period, control group institutions will implement the intervention in the same manner as those in the intervention group.

### Data collection

Data will be collected at three time points: At baseline; at a 10-week follow-up (Immediate post-intervention for intervention group and Pre-intervention for control group); and at a 20-week follow-up (Long-term post-intervention for intervention groups and Immediate post-intervention for control group). Baseline and immediate post-intervention data collection will consist of i) an electronic questionnaire through a link provided in a text message to the participants, ii) anthropometric measurements, iii) testing of cardiorespiratory fitness, and iv) wearable sensor technical measurements of physical activity and heart rate. At the long-term post-intervention follow-up, data collection will include only a modified questionnaire.

### Questionnaire

The questionnaires include a combination of items to assess the following descriptive factors of the study population, as well as potential confounders, and beneficial and adverse effects i) sociodemographic factors, i.e. age; sex; ethnicity; length of service; job title; and weekly working hours, ii) health and behaviours, i.e. musculoskeletal pain and pain-related work interference [28]; medicine use; smoking; general health [29, 30]; self-efficacy [31]; well-being [32]; and sleep behaviour [33], iii) self-rated physical capacity: cardiorespiratory fitness and muscle strength [34], iv) stress [35], and v) work environment factors, i.e. perceived physical exertion during work [36]; productivity [37]; psychosocial work environment [38]; single item work ability [39]; short-version perceived need for recovery [40]; and sickness absence and presenteeism [41, 42].

Need for recovery and productivity will act as secondary outcomes. Need for recovery will be determined using a short, three-item version: ‘At the end of my work day I am exhausted’; ‘I find it hard to show interest in other people, when I have just come home from work’; and ‘It takes me over an hour before I am fully recovered after a work day’. All items have five response categories: ‘Never’; ‘Rarely’; ‘Some of the Time’; ‘Most of the Time’; and ‘Always’ [40]. Productivity will be determined using one item: ‘On a scale from 0 to 10, where 0 is the worst job performance anyone could have at your job and 10 is the performance of a top worker, how would you rate your overall job performance on the days you worked during the past 4 weeks (28 days)?’ [47].

### Anthropometric measures

We will measure height (Seca 213; Seca GmbH, Hamburg, Germany) and weight (BC-418 MA body composition analyzer; Tanita, Tokyo, Japan), and calculate the body mass index (body weight [kg]/ (body height squared [m^2^])). In addition, we will determine fat percentage (BC-418 MA body composition analyzer; Tanita, Tokyo, Japan) and resting blood pressure (Omron M3 or Omron M6 Comfort; Omron Corporation, Kyoto, Japan).

### Physical activity and heart rate

#### Physical activity type and body postures

Physical activity type (i.e. moving, walking, running, bicycling, climbing stairs), body position (i.e. sitting, and standing), and number of steps will be measured using a thigh-worn AX3 accelerometer (3-Axis Logging Accelerometer; Axivity Ltd., Newcastle upon Tyne, UK) and processed using the validated Acti4 software [43–45].

The AX3 accelerometer generates measurements of linear acceleration in three dimensions with a dynamic range of ± 8 G, sampled with a precision of 13 bits at a sampling rate of 25 Hz. The AX3 accelerometers are initialised prior to recording, and data will be downloaded using the manufacturer’s software (OMGUI Version 1.0.0.30; Axivity Ltd).

One AX3 accelerometer will be mounted on the right thigh at the most muscular part of the quadriceps femoris, midway on the line between the anterior inferior iliac spine and the top of the patella [44]. The AX3 accelerometer will be mounted on the skin with adhesive tape (Hair-Set double-sided adhesive tape; 3 M Company, Maplewood, MN, USA) and secured with transparent adhesive film (Opsite Flexifix; Smith & Nephew plc, London, UK). We will ask the participants to wear the accelerometer around the clock during five working days.

#### Heart rate and heart rate variability measures

We will measure heart rate and heart rate variability using a Firstbeat Bodyguard 2 monitor (Firstbeat Technologies Ltd., Jyväskylä, Finland). The monitor measures the electrocardiogram at a sampling frequency of 1000 Hz, and the signal is processed to identify R-spikes and subsequently R-R intervals. The monitor has been validated for long-term measurements of heart rate in free living [46].

The Firstbeat Bodyguard 2 will be mounted with Ag/AgCl pre-gelled electrodes (Ambu WhiteSensor CMM-00-S/30; Ambu A/S, Ballerup, Denmark) below the right clavicle and at the left rib cage. We will download data from Firstbeat Bodyguard 2 using the manufacturer’s software (Firstbeat Uploader Version 3.1.2.0; Firstbeat Technologies Ltd., Jyväskylä, Finland). As for the accelerometer, we will ask the participants to wear the heart rate sensor around the clock during five working days.

### Cardiorespiratory fitness

Cardiorespiratory fitness will be assessed using the Ekblom-Bak submaximal test [47] performed on a cycle ergometer (Monark AB, Varberg, Sweden). The Ekblom-Bak test estimates cardiorespiratory fitness (VO_2max_) based on the difference in heart rate between an initial low standard workload and a subsequent higher ‘final’ workload. The test has shown good validity in a wide population range (Women: 21–86 years old with a VO_2max_ range of 19–62 ml/ min/kg; Men: 20–84 years old with a VO_2max_ range of 24–76 ml/min/kg [47]).

The test is initiated by having participants performing a standard workload of 60 revolutions/ minute at a resistance of 0.5 kp for 4 min. Heart rate is measured four times during the last minute (3:15, 3:30, 3:45, and 4:00) and the average of these four measurements is used as the initial heart rate. Subsequently, resistance is increased in steps with the aim of reaching a perceived exertion rating of approximately 14 on the Borg RPE-scale [36], and a heart rate between 120 and 150, or 110 and 140 beats/ minute for participants younger or older than 50 years, respectively. Perceived exertion is rated after 2 min at each step. If below 10 or 12, resistance is incrementally increased by 1 kp or 0.5 kp, respectively, for younger and older participants. When reaching the target exertion and heart rate, four measurements are collected during the last minute, with the average heart rate of these four measurements providing the final heart rate [47]. Cardiorespiratory fitness is calculated from equations described in [47].

### Primary and secondary outcomes

Differences between the intervention and the control groups in changes from baseline to 10-week follow-up will be evaluated for all primary and secondary outcomes. The primary outcome is the relative work time spent in MVPA, as determined by either heart rate (i.e. ≥60% of heart rate reserve) or accelerometer recordings (i.e. fast walking (≥130 steps/ minute), running, or stair climbing).

Furthermore, the study has four secondary outcomes: i) cardiorespiratory fitness, ii) resting heart rate during sleep, iii) perceived need for recovery; and iv) self-reported productivity. Figure 4 shows the SPIRIT schedule of enrolment, interventions, and assessments [22].

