### Statistical analysis

Evaluation of intervention effectiveness on the primary and secondary outcomes as well as the cost-effectiveness will be based on multilevel models, taking into account that the study design implies repeated measurements within each participant [57]. Conclusions about the effectiveness of the intervention with respect to the primary and secondary outcomes will be based on the group effect and its 95% confidence interval. The 95% confidence intervals for the incremental cost-effectiveness ratio will be estimated using bootstrapping (1000 bootstrap samples with replacement) [58]. All analyses will be performed according to the intention-to-treat principle [59]. Potential confounding factors (e.g. baseline differences between the intervention and control group in factors like age and BMI) will be adjusted for in the statistical analyses.

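### The effect is defined as a between-arm difference in change from baseline, with no commitment to adjust for the participant's own baseline value, which risks avoidable loss of precision and sensitivity to chance baseline imbalance

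*Protocol article*

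**What the plan says.** The section Primary and secondary outcomes fixes the comparison: "Differences between the intervention and the control groups in changes from baseline to 10-week follow-up will be evaluated for all primary and secondary outcomes". Relative work time in MVPA, from heart rate or accelerometer recordings, is the primary outcome.

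The section Statistical analysis names the model class, "multilevel models, taking into account that the study design implies repeated measurements within each participant", and says that conclusions "will be based on the group effect and its 95% confidence interval". Its adjustment rule is: "Potential confounding factors (e.g. baseline differences between the intervention and control group in factors like age and BMI) will be adjusted for". The baseline value of the outcome is neither named nor excluded.

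The data for adjustment will exist. Under Data collection, both the baseline and the immediate post-intervention rounds include "wearable sensor technical measurements of physical activity and heart rate". The control group's week-10 round is labelled pre-intervention there, and the stated week-10 contrast presupposes the same measurements.

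The section Power calculation works on isometric log-ratio (ilr) values. It refers to before-and-after measures, but names no estimator and gives no before-after correlation.

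**The concern.** When a multilevel model treats baseline and week 10 as two outcomes and lets each arm have its own baseline mean, the complete-data difference in change is the plain change-score difference. That fixes the slope on baseline at 1, which is efficient only if the two measurements correlate almost perfectly. The outcome here is a rare behaviour recorded over five working days, so a correlation near 1 should not be taken for granted.

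Two things are at stake. The confidence interval on which the conclusion rests would be wider than it need be. And if one arm happens to start low, part of its expected drift back towards the mean is counted as intervention effect. With about 14 institutions, some imbalance is likely. The same contrast applies to all four secondary outcomes.

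**Working it through.** **Inputs from the article (Power calculation).** SD 1.10 on the ilr scale, ICC 0.05, cluster size 10, drop-out 30%, about 14 institutions, total 132, power 0.80, significance level 0.05 (taken as two-sided). Expected completers per institution: 10 × 0.70 = 7, so 7 × 7 = 49 per arm.

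**Assumed.** The correlation rho between baseline and week 10, with equal variance at both visits.

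**The article's own figure.** The total of 132 cannot be reproduced, because neither rho nor the ilr shift equal to 5 min/day is given. As a trial reading, take the shift from 1.24 to 6.24 min in an assumed 450-minute workday:
- Shift: [ln(6.24/443.76) − ln(1.24/448.76)]/√2 ≈ 1.15.
- Per arm, variance factor 1: 2 × (1.10 × 2.80/1.15)² ≈ 14.3, rounded up to 15.
- Design effect: 1 + 9 × 0.05 = 1.45.
- Change score at rho 0.5 (factor 2(1 − 0.5) = 1): 2 × 15 × 1.45/0.70 ≈ 62.
- Change score at rho 0 (factor 2): about 124.

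Neither gives 132, so the figure does not show which contrast was powered.

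**Variance, ignoring clustering.**
- Change score: 2σ²(1 − rho).
- Baseline-adjusted: σ²(1 − rho²).
- Ratio, adjusted to change: (1 + rho)/2. Saving: (1 − rho)/2.

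The last column applies only if the stated 0.80 belongs to the change contrast. It is Φ(2.80/√ratio − 1.96).

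| rho | ratio | variance saving | CI narrower by | power after adjustment |
|---|---|---|---|---|
| 0.3 | 0.65 | 35% | 19% | 0.935 |
| 0.5 | 0.75 | 25% | 13% | 0.899 |
| 0.7 | 0.85 | 15% | 8% | 0.860 |
| 0.9 | 0.95 | 5% | 3% | 0.820 |

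Below rho 0.5, 2(1 − rho) exceeds 1, so the change score is less precise than ignoring baseline.

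**With clustering, rho 0.5.** Change scores remove stable institution effects, so the saving shrinks.
- Simulation of 14 institutions with 7 completers each, same correlation at both levels: SD of the estimate 0.250 (change) against 0.219 (adjusted). Variance ratio 0.767, saving 23%.
- Institution means correlated 0.9 over time: 0.223 against 0.203. Ratio 0.822, saving 18%.
- Model-based variances with a fully stable institution effect and unit outcome variance: 0.0408 for group-by-time, identical to the change score, against 0.0330 with a common baseline mean. Saving 1 − 0.0330/0.0408 ≈ 19%.

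The interval narrows by 1 − √0.822 ≈ 9% up to 1 − √0.75 ≈ 13%. At individual rho 0.7 with institution-level 0.9, the ratio is 0.896, a saving of about 10%.

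**Sensitivity to imbalance.** Given an observed baseline difference D, the change-score estimate is shifted on average by −(1 − rho)D. The standard error of D is 1.10 × √(2 × 1.3/49) ≈ 0.253, where 1.3 = 1 + 6 × 0.05. An imbalance of one standard error at rho 0.5 therefore moves the estimate by about 0.127 ilr units, half of the 0.250 standard error of the estimate itself.

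**The case against.** The strongest reply is that the article names a quantity, not an estimator. Under randomisation, a baseline-adjusted model and a common-baseline repeated-measures model both estimate the difference in change, and the words group effect would fit an adjusted model. The covariate list is open, the analysis scale is ilr, and a separate analysis plan may settle the form. A reader might infer that the trial will analyse raw change scores with baseline MVPA excluded. The article does not say that, and this part of the reply stands.

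It does not dispose of the point. The stated contrast, the repeated-measures wording and the before-and-after design together read most naturally as group-by-time. The only adjustment rule given is tied to observed baseline differences, so even on a generous reading baseline MVPA would not be fixed in advance.

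Second, the remedy is a trade-off here. Institutions learn their arm before baseline data collection (Randomisation and blinding), workers join voluntarily (Study population), and the article names selection bias as its main limitation. If baseline differences are systematic and stable, a change score removes them and baseline adjustment under-corrects. This stands, and is why the change contrast should be kept as a sensitivity analysis.

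Third, the size is uncertain. Rho is not given, and the large between-subject spread (SD 2.90 around 1.24 min/day) does not itself show a low correlation over time. The power gain also depends on what 0.80 refers to. If it already assumed adjustment, adjusting gains nothing over the plan; an unadjusted change contrast would instead fall short, at Φ(2.80 × √0.75 − 1.96) ≈ 0.68 for rho 0.5, ignoring clustering.

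**Conclusion.** The point holds in limited form. The article defines the effect as a difference in change and does not commit to adjustment for the participant's own baseline. If fitted as group-by-time with free baseline means, the analysis gives up precision that data already planned would supply, and its estimate moves with chance imbalance.

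The size rests on an assumed correlation. The variance saving is about 35% to 5% for rho 0.3 to 0.9 ignoring clustering, and about 18% to 25% at rho 0.5. No power gain can be claimed from the article, since it does not say which contrast has power 0.80.

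Two stronger readings are not supported. One is that the trial loses a quarter of its precision: that needs rho 0.5, no allowance for clustering, and a model form the article does not fix. The other is that the change contrast is biased: under randomisation it is unbiased on average, and the shift shown above is conditional on the realised baseline difference.

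This is worth correcting before the data are analysed, but it does not invalidate the design.

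**What to change.** In Primary and secondary outcomes and in Statistical analysis, state that the primary effect is the between-arm difference in week-10 MVPA on the analysis (ilr) scale, adjusted for the participant's own baseline value, with a random institution effect. Fix this covariate in advance, whatever baseline difference is observed, and use the same form for the four secondary outcomes.

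Report the unadjusted difference in change as a sensitivity analysis, with the reason: allocation is known before baseline measurement and participation is voluntary, so baseline differences may be systematic. For the same reason, prefer the baseline covariate to a model that forces equal baseline means, which would write into the model an equality that the enrolment process does not guarantee.

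The cost is a sentence or two of analysis wording and one model degree of freedom, with no new data or participants. Participants without a baseline value drop out of the covariate form unless the model handles them, so the text should say how they are treated.

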**Fig. 4 Fig4:**
[figure not shown]
Standard Protocol Items: Recommendation for Interventional Trials (SPIRIT) schedule of enrolment, interventions, and assessments. W = Workshop; CV = Consultant visit; FU = Follow up; MVPA = Moderate to Vigorous Physical Activity. *Randomisation carried out at childcare institution level before baseline measurements. **The study uses a wait-list design; control group institutions will receive the intervention after the intervention group

### Economic evaluation

The economic evaluation aims to determine the cost-effectiveness of the intervention in terms of cost (from the employer’s perspective) per increment in work time spent in MVPA. Costs of the intervention will include costs related to implementation and operation, specifically:

#### Staff time

Participation in intervention activities for workers (workshops, and kick-off meeting for the project), and Trio (workshops, kick-off meeting for the project, and time spent on planning the logistics of implementing the intervention) will be assessed based on registration of attendance. Costs for participants and supervisors will subsequently be estimated based on their average yearly gross salaries, including overhead.

#### Consultant time

Time spent on delivery of the intervention (workshops, kick-off meeting, and workplace visits) will be assessed by asking the work environment consultants how many hours they spent on these activities, including preparations. The number of working hours will be valued by using their hourly fee, including overhead.

#### Consumables

Materials, such as printouts and posters, as well as fruit/snacks/coffee consumed at meetings will be noted. Costs will be valued using invoices.

For the control group, only costs related to participation in the joint kick-off meeting will be included.

The total intervention costs for the employer will be estimated and compared between the intervention and control group. The incremental cost-effectiveness ratio will be calculated by dividing the mean difference in costs (incremental cost) between both groups by the difference in effects (incremental effect) on the primary outcome measure.

In addition, sickness absence will be measured by questionnaire from the participants in the control and intervention groups at baseline and 10-week follow-up.

Costs associated with absenteeism will be estimated using the Friction-Cost approach [48]. A friction period of 4 weeks will be assumed, as the Danish social security system takes over costs after 4 weeks of sickness absence. Furthermore, an appropriate elasticity factor will be used. Health-related productivity losses will be valued using gross yearly salaries of the participants converted to a daily cost based on assumed numbers of working days per year.

### Process evaluation

Before the intervention starts, we will collect information addressing facilities at the childcare institutions, including possible areas for the Goldilocks-games and accessibility to these areas. Further, we will collect information about readiness for change among employees at the childcare institutions.

To assess the extent to which the intervention is implemented as intended, a process evaluation will be conducted. The process evaluation will follow the principles described by Steckler and Linnan (2002), and Ferm and colleagues (2018) [49, 50]. The process evaluation will assess how the intervention was delivered (Fidelity) and received (Receipt) [49].

Fidelity includes three measures i) Dose (the number of intervention components delivered); ii) Content (if the components are delivered in accordance with the workshop manual); and iii) Quality (the self-rated performance of the deliverer). Receipt includes two measures i) Participation (number of participants attending the two workshops); and ii) Responsiveness (satisfaction and motivation among the participants). Following each workshop, the work environment consultants will assess dose, content, quality, and participation in a customised questionnaire. Responsiveness will be assessed by questionnaire to the participants following the intervention.

Additionally, we will collect information regarding facilitators and barriers for implementing the intervention through semi-structured interviews with managers during the consultant visits. These interviews will provide information on contextual factors for each of the childcare institutions that could have influenced the implementation or the effect of the intervention, e.g. occurrence of major organisational changes during the intervention period, or concurrent activities with a likely impact.

